**Follow-Up**

The exploratory RCT and definitive RCT differ in follow-up assessments. While in the exploratory RCT, the final post intervention assessment by independent assessors is 1 week after the completion of PM+, in the definitive RCT the final outcome measures will be taken at 3 months after the final PM+ session. As mentioned, 5 participants will also be invited to participate in semi-structured interviews. These interviews will be conducted within 4 weeks of the final outcome assessment (i.e within 4 months of the intervention). All participants will be told that they may contact their local primary health care facility in case they need future support. Names and contact details of the field coordinator and local site PI will be provided on the consent form of which all participants receive a copy.

Depending on the adverse event, follow up may require additional tests or medical procedures as indicated, and/or referral to the general physician or a medical specialist. All adverse events will be followed until specialist care (including referrals, additional tests or medical procedures) is in place for the client, or until a stable situation has been reached.

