Of note, in Nairobi, each primary health care facility, and sub-country hospital, employs a Community Health Extension Worker (CHEW), who coordinates referrals from within the community and to ensure patients are followed-up by nurses and/or Community Health Workers (CHWs). The CHEWs from each health facility of the project is working with will be receiving a small additional allowance for their involvement in the research project. Their involvement will be to monitor that referred patients are actually seen when they are referred to the enhanced usual care or to the subcounty office. The CHEW will complete a basic form to monitor the date, time of the appointments and whether they occurred.

Throughout the trial, we will carefully keep track of the types and amount of support received through SRI items (see measures section above).

*PM+ providers and protocol adherence:*

PM+ providers will be female CHWs, who were recommended by the Ministry of Health, based on those that have shown high performance in their regular health work in the communities. After receiving the recommendation, CHWs will be selected based on individual interviews.

PM + providers will meet the following criteria:

- High school diploma (form 4 level of education or above);
- Reasonable proficiency in both Kiswahili and English language – written and verbal;
- 1-year training post-secondary school as CHWs or health related career;
- 2-years and above experience in community work;
- Already working as a CHW within a given geographical area.

PM+ providers will receive 2 weeks of training. In addition, one professional supervisors will be employed for each of the 3 health facility areas. Protocol adherence will be ensured by the supervisors and weekly group supervisions of the CHWs (Murray et al, 2011). Supervisors will then receive their own supervision and on-the-job training in supervision skills by the project lead consultant, who is a qualified counselling psychologist and available for any specific and/or urgent cases where either the CHWs themselves, the supervisors or any of the clients in the program need support. This will take place weekly as well.

To ensure adherence to the PM+ manual and ensure fidelity of interventions, 10% of all PM+ sessions will be attended by the supervisor, using a checklist to ensure basic elements of the PM+ intervention have been followed as required.

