The CHWs, who will provide the PM+ intervention, already visit specific households as a standard part of their work with health facilities in the area. A local security assessment has indicated that it will be safe for screeners, assessors and CHWs to work at the household level.

All assessors and PM+ providers will receive pre-paid phone credit by the project to facilitate constant communications with each other and with the local World Vision office.

At the end of the study (at 4-5 months after inclusion), participants in the TAU condition will also be offered the PM+ intervention, if still indicated. If after the project, participants continue to experience psychological problems they will be offered additional support through aforementioned referral hospital, see above).

All adverse reactions and serious adverse events (SAEs) reported spontaneously by the subject or observed by the investigators or other staff members will be recorded by the research team. We consider an event a SAE if it is an undesirable experience occurring to a subject during the study, whether or not considered related to the research procedure. Although it is unlikely that SAEs would occur given the nature of the intervention, all adverse events and SAEs will be reported to the local independent advisory board.

The local advisory board will consist of: an independent medical officer (chair), an independent counselling psychologist with community mental health experience, the site principle investigator, and the clinical supervisor. All serious adverse events (SAE) and adverse events (AE) will be reported by the local principle investigators or supervisor to this advisory board. The chair or a nominated person from the advisory board will review SAEs within 48 hours.

Terms of reference of the advisory board are . 1. to establish rules and procedures governing its own meetings, consistent with the research protocols and standard; 2. to review SAEs within 48 hours, and all (S)AEs once a month and determine whether an (S)AE is likely to be related or unrelated to the intervention. 3 as necessary, recommend appropriate action in respect of ongoing trial conduct (such as referral to specialized care or installing extra assessment points for monitoring participants), and 4. follow-up to know whether recommended actions have taken place

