This study uses 5 key questions of the WHO Violence Against Women Instrument (WHO-VAW, WHO, 2003) as developed for use in the WHO Multi-Country Study on Women’s Health and Domestic Violence (WHO, 2005) and will adhere to the WHO guidelines for the conduct of violence against women research, which stress confidentiality and privacy, and availability of referral for psychological and social help. Before asking these 5 questions, women will be reminded that they are free to skip any questions. To ensure confidentiality, the interviewers are trained that of they are interrupted they will either terminate the interview, or to stop asking about violence and to move on to another, less sensitive topic until privacy can be ensured.

Another concern may involve the fact that participants in PM+ will receive treatment, whereas participants in TAU will not receive PM+. However, PM+ is a new intervention in this population, and although the efficacy of its main cognitive behavioral therapy components has been established in other populations (Dua et al., 2011; Tol et al., 2013; WHO, 2010b), a RCT is the necessary step for establishing effectiveness. In addition, participants in TAU will not be withheld care, but rather will have access to enhanced TAU. If, during the study participants in either arm of the study show severe psychiatric disorders or problems (e.g., suicidality) that require immediate treatment and follow-up, they will be referred to the relevant referral hospital.

The study is done in a low-income context, in which many individuals are exposed to multiple stressors and traumatic events. To test the utility of the PM+ protocol in real-world settings, it must be tested in situations in which it is intended to be implemented where there are ongoing stressors, uncertainty, adverse life events, etc. The current study is a necessary next step to test whether an intervention such as PM+ may be feasible and acceptable in such context with ongoing stressors and uncertainty. PM+ is based on evidence-based psychological techniques, that have been proven effective in more stable settings (WHO, 2013). Evaluating the intervention for delivery via non-specialist CHWs and testing their training and supervision procedures has to be carried out in real-life settings to provide meaningful information for implementation and scale-up.

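### The adverse-event rule lets follow-up end at referral with the outcome unrecorded, and this is likely to affect the graver events

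*Protocol*

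**What the plan says.** The Follow-Up section of the protocol sets the stopping rule. Its first condition reads "All adverse events will be followed until specialist care (including referrals, additional tests or medical procedures) is in place for the client". A second clause then offers another end point: "or until a stable situation has been reached". The two conditions are alternatives, and the parenthesis treats a referral as a form of specialist care.

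Three places say which problems are referred. The Ethics section, for either arm, covers severe psychiatric disorders or problems such as suicidality "that require immediate treatment and follow-up, they will be referred to the relevant referral hospital". The enhanced treatment-as-usual (TAU) text in Methodology says the same for the TAU arm. Safety Considerations does so for urgent psychiatric problems arising during treatment.

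Four further rules deal with what happens once an event has occurred:

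- Safety Considerations, recording: adverse reactions and SAEs "reported spontaneously by the subject or observed by the investigators or other staff members will be recorded by the research team".
- Safety Considerations, reporting: "all adverse events and SAEs will be reported to the local independent advisory board".
- Safety Considerations, board's terms of reference: "review SAEs within 48 hours, and all (S)AEs once a month and determine whether an (S)AE is likely to be related or unrelated". The board also recommends action where it sees a need, and its last listed task is "follow-up to know whether recommended actions have taken place".
- Methodology, enhanced TAU: for referred women, "The CHEW will complete a basic form to monitor the date, time of the appointments and whether they occurred".

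**The concern.** A follow-up rule for adverse events should tell the trial how each event ended. This one can be satisfied by a step in the care pathway. An event that needs no specialist is followed to stability. An event that leads to a referral may be closed once the referral is in place, whatever happens next. Because suicidality and severe psychiatric problems are referred, the early closing point is likely to apply where the result matters most for judging safety.

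Two other provisions make this more than a formality. Safety Considerations obliges the principal investigator to inform participants and the WHO ethics committee if the disadvantages of taking part appear significantly greater than foreseen, and that judgement depends partly on how events ended. Quality Assurance dispenses with a data monitoring and safety board, so oversight falls to the local advisory board. That board can review only the outcomes it is given.

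**Working it through.** The protocol states no figure on this point, so the check is a reading of the rules side by side. Each is tested on one question: does it require the outcome of a referred event to be recorded?

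| Provision | What it requires | Outcome of a referred event required? |
| --- | --- | --- |
| Follow-Up, first alternative | Follow until specialist care, including a referral, is in place | No |
| Follow-Up, second alternative | Follow to a stable situation | Not needed once the first is met |
| Safety Considerations, recording | Record events reported spontaneously or observed | Only if a later development is itself reported or seen |
| Board terms, review | SAEs within 48 hours, all events monthly; judge relatedness | No |
| Board terms, action | Recommend action, which may include extra assessment points | At the board's discretion |
| Board terms, check | Confirm that recommended actions took place | No |
| CHEW form | Date, time and whether the appointment occurred | No |
| Scheduled assessments | GHQ-12, WHODAS and PCL-5 after treatment and at 3 months; service-use items at 3 months | No; they measure symptoms, functioning and service use |

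No row contains a requirement to record whether a referred event resolved, continued, led to admission or ended in death.

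**Illustration of the time left open.** Methodology places the post-intervention assessment 7 weeks after the pre-intervention assessment and 1 week after session 5. The final assessment of the definitive trial is 3 months after session 5, taken here as 13 weeks.

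- Session 5: 7 − 1 = 6 weeks after baseline.
- Final assessment, definitive trial: 6 + 13 = 19 weeks. This fits the 4–5 months after inclusion given in Safety Considerations for the end of study.
- Assumed event in week 2 with a referral in place by week 3: 19 − 3 = 16 weeks to the final assessment.
- The same event in the exploratory trial, whose last assessment is at week 7: 7 − 3 = 4 weeks.

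Weeks 2 and 3 are assumed timings. The figures show how long an event could stay closed with no outcome. They do not say how often that would happen.

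**The case against.** Several points on the other side stand.

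- **Worsening or death after referral can still be recorded.** Safety Considerations counts any undesirable experience during the study as an SAE, related or not. A later admission, deterioration or death is such an event, and closing the first one does not switch that rule off. A reader might infer that no rule could record a death or worsening, and the text does not support that. The weakness is that capture is passive: it depends on the woman reporting the event or a staff member noticing it.
- **Referred women stay in the trial.** Nothing removes them from the scheduled assessments, so distress, functioning and hospital use would still be measured within the 16 weeks. Those instruments do not record how an event ended, however, and a woman who had died or was still in hospital could miss the visit.
- **The board may ask for extra assessment points.** This is a real safeguard, but a discretionary one.
- **A referral *in place* may mean more than a referral made.** The CHEW checks that referred women are actually seen. Even so, a kept appointment is not an outcome.
- **The link to severity is an inference.** Follow-Up also mentions referral to a general physician, so milder events can meet the first condition too.

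A reader might go further and conclude that harms cannot be reported by arm, or that the rule biases the comparison of PM+ with TAU. Neither follows. The sentence governs how long an event is followed, the occurrence of events is recorded regardless, and counts by arm remain possible. Tabulation by arm is commonly left to a statistical analysis plan, which is not shown here. Hospital referral of severe problems applies in both arms, and nothing in the protocol shows a difference between them.

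It can also be said that an outcome field is a matter for forms. That would carry weight if the protocol were silent, but it fixes a stopping rule, and a form designed to that rule could properly omit the outcome.

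**Conclusion.** The concern holds in a limited form. As written, the protocol allows an adverse event to be closed once a referral or other specialist care is in place, without its outcome being known. No other provision requires that outcome to be recorded. The graver events are likely to be the ones affected. That rests on the referral rules for suicidality and severe or urgent psychiatric problems, not on any count.

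The number of events affected cannot be derived, because the protocol gives no event rate and says only that SAEs are unlikely. The effect is on the completeness of the safety record. Efficacy data, event counts and treatment are not touched. The defect is modest but worth correcting, because an outcome not collected during the trial may not be recoverable at analysis.

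**What to change.** Reword the sentence in Follow-Up so that it separates data capture from care. For every referred adverse event, the outcome (resolved, ongoing, admitted, died, unknown) is recorded until the event is resolved or stable, or until the participant's last scheduled study assessment, whether or not a referral is in place. That last assessment is 1 week post-treatment in the exploratory trial and 3 months post-treatment in the definitive trial. Include the recorded outcome in the board's monthly review.

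The listing to the board need not be split by arm. The site principal investigator and the clinical supervisor sit on that board, and a split would show them accumulating comparative data.

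The change alters no referral or treatment decision. It costs one sentence, one form field and a few extra contacts, for which the CHEW, who already tracks referred women, is a natural route. The workload could exceed expectation: the SAE definition in Safety Considerations has no seriousness criterion, so in a population exposed to continuing adversity many experiences could qualify. Limiting the requirement to referred events helps to contain this.

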**Data Management and Statistical Analysis**

The data, as collected by the interviewers (Study Phases 2 and 4) and independent assessors and PM+ providers (Study Phases 1 and 3) will be safely stored at the World Vision office of the field coordinator at Rituta ADP

Quantitative data will be coded and the identifying key (a list connecting names to numbers) will be kept in a separate, secure locked location in the field coordinator’s office. The data will be entered into a data-analytic computer program (e.g., SPSS), without the identifying key. Data will only be available to the members of the project group. No attributable data will be used in publications. The investigators will analyze the data, and both positive and negative trial results will be disclosed. Results will be submitted for publication to peer-reviewed scientific journals.

The qualitative research will follow thematic analyses as described above.

For the RCT’s, both intention-to-treat analysis and completers’ analyses will be carried out. To measure comparisons at baseline between the two treatment groups t-tests will be conducted for continuous variables and chi-squared test for categorical ones. Repeated measurement analysis will be carried out to assess differential change over time in mean GHQ-12 scores between groups. We will add the following covariates at baseline to examine subgroup effects: education, employment, and severity of symptoms. All analyses will be carried out in SPSS, with p-levels of <.05 indicating statistical significance.

For the economic evaluation, we follow the approach used before in a similar trial (Buttorff et al, 2012). The number of days with reduced working hours because of poor health will be calculated from the WHODAS-12. Participants’ self-reported their health-care utilization, medication use and out-of-pocket payments will be measured with the items derived from the SRI at post treatment and 3 months follow-up.

For the costs analysis, two types of costs measured at post-treatment and at the 3-months follow-up will be estimated based on SRI scores: health-system costs (i.e., costs related to the intervention itself and associated medications and/ or clinical investigations) and the "time costs" for the subjects and their families (i.e. time spent travelling to, waiting for or receiving care, plus the wages from any days of work lost). The human resource use associated with the community health workers employed in the intervention will be estimated by multiplying the time a participant in PM+ has contact with a CHW by the per-hour cost of the CHW.

Costs, scores and days-of-work data from each follow-up will be summed to give totals for the 3 months post-treatment. Differences between PM+ and TAU, will be assessed using generalized linear models. Cost–effectiveness acceptability curves showing the probability that an intervention remains relatively cost–effective at increasing monetary values, will be developed.

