   3. *Pre-assessment.* Next, pre-assessment is completed by administering the Life Events Checklist (LEC; (Gray, Litz, Hsu, & Lombardo, 2004)), the PTSD Checklist for DSM-5 (PCL-5, Weathers et al, 2013) and items derived from the Service Receipt Inventory (SRI; (Chisholm, Knapp, et al., 2000)).
2. Randomization
   1. Randomization will be carried out by an independent trial unit (at University of New South Wales) Randomization will be performed using computerised software on a 1:1 basis.
3. PM+ Intervention
   1. *Appointments.* CHW who will make contact with participants for treatment to begin. The first PM+ session will be scheduled within a few days and no longer than one week after the baseline assessment. This therapist will plan five consecutive meetings with the participant.
   2. *Additional instrument.* At the start of PM+ and at the beginning of every session the Psychological Outcome Profiles instrument (PSYCHLOPS; (Ashworth, 2004)) will be administered. This instrument, in contrast to above named instruments will be administered by the therapist *to assess and monitor* progress on problems for which the person seeks help.
4. Post intervention assessment
   1. *1-week follow-up.* The post-intervention assessment (WHODAS, GHQ-12, PCL-5) will be scheduled 7 weeks after the pre-intervention assessment (i.e., 1 week after the 5^th^ PM+ session).
   2. *3-month follow up.*  The follow-up assessment - with the same questionnaires plus the life events measure (LEC) and SRI items but without the treatment satisfaction questionnaire - will be scheduled at 3 months after the 5^th^ PM session.

All instruments will be administered by trained research staff blind to the allocation status of the participants. All independent assessors will receive a five day training in administering the instruments, in general interview techniques, and in responding to participant distress, including, as mentioned, psychological first aid.

*Statistical power and sample size*

Since Study Phase 1 is a small exploratory RCT with 40 participants (20 participants per group), that does not aim to detect statistically significant differences in effectiveness, no power calculations have been (or should be) carried out.

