Data on socio-demographic information (sex, age, education, marital status and work status) will be collected through questions A1-A5 of the WHO Disability Assessment Schedule 2.0 (WHODAS; [WHO, 2010a](#_ENREF_26)), which will be administered first. The WHODAS is a generic assessment instrument assessing health and disability. It is used across all diseases, including mental neurological and substance use disorders. It is simple to administer and applicable across cultures and can be used in all adult populations. WHODAS covers six domains (cognition, mobility, self-care, getting along, life activities, participation). It assesses difficulties people have due to their illness across these domains during the last 30 days. Difficulties are scored as none, mild, moderate, severe, or extreme. We will use the 12-item interviewer administered version. The WHODAS has been validated in Kenya (Chepngeno-Langat et al., 2011).

In analyses of Study Phase 3 data, the WHODAS will also be used to compute Quality Adjusted Life years, which is a measure of disease burden, for Study Phase 3 (Buttorff et al, 2012). Reference data for the female Kenyan population will be derived from the World Health Survey, in which Kenya was included (<http://apps.who.int/healthinfo/systems/surveydata/> index.php/catalog/80).

1. GHQ-12: distress

The primary outcome is level of psychological distress as measured by the General Health Questionnaire (GHQ-12; Goldberg & Williams, 1988; Jenkins et al., 2013) at 3 months follow-up (i.e., 3 months after the 5^th^ PM+ session). The GHQ-12 consists of 12 questions that are scored on a 4-point Likert scale ranging from 0 to 3..The total GHQ-12 score is obtained by summing up the scores of the individual items and ranges between 0-36 with higher scores representing higher levels of distress. When used as a screening tool, the GHQ-12 is usually scored bi-modally (i.e. - 0-0-1-1)., and ranges between 0-12. In a previous study in Kenya, a cut-off of higher than 2 has been reported to indicate clinical levels of distress (Jenkins et al., 2013).The GHQ has been widely used across low- and middle income countries, including Kenya (Jenkins et al., 2013).

1. LEC: exposure to potentially traumatic events (life events)

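### The primary outcome is GHQ-12 at 3 months, but the only stated effectiveness analysis tests differential change over time and names no 3-month contrast

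*Protocol*

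**What the plan says.** **The target.** Under Measures (GHQ-12), the Methodology section states: "The primary outcome is level of psychological distress as measured by the General Health Questionnaire", measured "at 3 months follow-up (i.e., 3 months after the 5^th^ PM+ session". The outcome is a continuous score: "The total GHQ-12 score is obtained by summing up the scores of the individual items and ranges between 0-36". The sample size paragraph compares a 50% with a 30% reduction at 3 months, and the Follow-Up section places the definitive trial's final outcome measures at the same point.

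**The occasions.** In the definitive trial GHQ-12 is obtained three times: at baseline, where it is also the entry screen; at post-treatment ("The post-intervention assessment (WHODAS, GHQ-12, PCL-5) will be scheduled 7 weeks after the pre-intervention assessment"), which is 1 week after the last session; and at 3 months.

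**The analysis.** Data Management and Statistical Analysis gives one sentence on the effectiveness comparison: "Repeated measurement analysis will be carried out to assess differential change over time in mean GHQ-12 scores between groups". The sentences around it add:

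- populations: "both intention-to-treat analysis and completers’ analyses will be carried out"
- covariates: "We will add the following covariates at baseline to examine subgroup effects: education, employment, and severity of symptoms"
- the significance rule, for all analyses: "with p-levels of <.05 indicating statistical significance"

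Nothing there singles out the 3-month visit, and baseline severity is introduced for subgroup effects, not for adjustment.

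**The concern.** The primary outcome asks whether the arms differ at one time point. The analysis asks whether their trajectories differ. With three occasions, trajectories can differ because the arms separate at 1 week and have come together again by 3 months. A significant result would then not answer the primary question. For a five-session intervention, durability is what a 3-month endpoint is there to test, so the distinction matters.

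There is a second, smaller matter. If baseline GHQ-12 is treated as one of the repeated outcomes, each comparison becomes a difference in change from baseline. That is less precise than adjusting the follow-up score for baseline, unless the correlation between visits is high.

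**Working it through.** **Inputs from the protocol.** 173 women per arm, 30% expected attrition at 3 months, three GHQ-12 occasions, two-sided 5% level. Completers per arm: 173 × 0.7 = 121.

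**Assumptions not in the protocol.** SD = 1 at each visit, so effects are in SD units; the same correlation r between any two visits (compound symmetry); r = 0.3 and 0.5, with 0.7 as a check. The protocol gives no SD and no correlation.

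**The plan's own figures.** The protocol states no power for the repeated-measures analysis, so there is none to reproduce. Its sample size compares 50% with 30%; the odds ratio (0.5/0.5)/(0.3/0.7) = 2.33 agrees with the stated 2.3. The stated 133 per group did not reproduce (the usual two-proportion formula gives 153). That is a separate matter and nothing below uses it.

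**Step 1: group-by-time test, effect gone by 3 months.** The two between-arm differences in change (post minus baseline, 3 months minus baseline) have covariance (2/n)(1−r)[[2, 1], [1, 2]]. For effects (d1, d2) the noncentrality is

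λ = (n/2) × (2d1² − 2d1d2 + 2d2²) / (3(1−r)).

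With n = 121, d1 = 0.4, d2 = 0: λ = 60.5 × 0.32 / (3(1−r)), which is 9.2 at r = 0.3 and 12.9 at r = 0.5. The noncentral F on 2 and 480 df gives rejection probabilities of 0.78 and 0.90 (0.99 at r = 0.7). A 3-month contrast rejects in 5%, because its null hypothesis is true.

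**Step 2: the same test, sustained effect.** With d1 = d2 = 0.4 the bracket is 0.32 − 0.32 + 0.32 = 0.32 again, so λ and the power are the same as in step 1. The test gives equal weight to an effect that lasts and to one that has disappeared.

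**Step 3: 3-month contrasts, effect 0.4 SD.** Standard error = √(2v/n), with v = 1 − r² if adjusted for baseline and v = 2 − 2r for a change score. At r = 0.3, adjusted: √(2 × 0.91/121) = 0.123; 0.4/0.123 = 3.26; power = Φ(3.26 − 1.96) = 0.90.

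| r | Group-by-time test, faded or sustained 0.4 SD | 3-month change score, sustained | 3-month baseline-adjusted, sustained |
|---|---|---|---|
| 0.3 | 0.78 | 0.75 | 0.90 |
| 0.5 | 0.90 | 0.875 | 0.95 |
| 0.7 | 0.99 | 0.98 | 0.99 |

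The variance ratio of adjusted to change score is (1 − r²)/(2 − 2r) = (1 + r)/2, that is 0.65, 0.75 and 0.85.

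**Step 4: simulation check** (4,000 trials per setting). For 0.5 SD at post-treatment and zero at 3 months, the group-by-time test rejected in 0.930, 0.986 and 1.000 of trials at r = 0.3, 0.5 and 0.7; the baseline-adjusted 3-month contrast rejected in 0.050, 0.047 and 0.052. With no effect at any visit, the group-by-time test rejected in 0.044 to 0.052.

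**Step 5: other readings of the sentence.**

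- A baseline-adjusted average over both follow-up visits rejects for a fully faded 0.5 SD effect with probability 0.74 to 0.90 (r = 0.3 to 0.7).
- A linear slope (visits taken at weeks 0, 7 and 19) rejects for that effect in only 0.09 to 0.14 of trials, but its power for a sustained 0.4 SD effect is 0.66 to 0.95.

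Neither estimates the difference at 3 months.

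**The case against.** The strongest reply is that the sentence describes a family of models and fixes no test. It covers both trials, and the exploratory trial has no 3-month visit according to the overview of Phases 1 and 3 and the Follow-Up section; there the same words yield a single change comparison. Contrast, baseline handling and covariance structure are often left to a statistical analysis plan, which may exist here. A reader might infer that the protocol declares a two-degree-of-freedom omnibus test. It does not: that is the plain reading of differential change over time, but only a reading, and under a linear slope a faded effect is rarely flagged.

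Three further inferences also go beyond the text.

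- *That a faded effect would be declared a success.* The protocol has no success rule beyond the general 5% convention, and claiming success without a 3-month difference would contradict its own primary outcome. The wording leaves this open; it does not prescribe it.
- *That precision is certainly lost.* This depends on the correlation, and a repeated-measures model that constrains the baseline means to be equal recovers essentially the adjusted precision. Baseline severity is also listed as a covariate, though for subgroup effects.
- *That the intention-to-treat analysis collapses into a completers' analysis.* Women with a missing visit drop out only if SPSS repeated-measures GLM is used. The protocol names SPSS but not that procedure, and it lists the two analyses as distinct. The 30% is attrition at 3 months, not the share of women with any missing visit.

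Nor is the analysis invalid: with no effect at any visit its error rate is nominal. What the reply leaves standing is that the protocol fixes the primary time point in one section and, in another, states a hypothesis that is not about that time point. That is a mismatch within the document, not only detail deferred.

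**Conclusion.** The point holds as a mismatch between the declared primary outcome and the only effectiveness analysis stated. Its practical size rests on the group-by-time reading, 121 completers per arm, compound symmetry and r of 0.3 to 0.5. Under these, about 78% to 90% of trials would be significant for a 0.4 SD effect that has gone by 3 months, against 5% for a 3-month contrast. This part does not depend on a low correlation: at r = 0.7 the figure is 99%. The power gain for a sustained effect (0.78 to 0.90 rising to 0.90 to 0.95) does depend on it and is almost nil at r = 0.7. The missing-visit argument is conditional on the software procedure and carries no weight in this conclusion. It should be fixed: the text leaves open which result answers the primary question, but the comparison is valid and the remedy is short.

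**What to change.** In Data Management and Statistical Analysis, state that:

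- the single primary test is the PM+ minus TAU difference in GHQ-12 at 3 months, adjusted for baseline GHQ-12, in all randomised women;
- it is estimated, for example, from a likelihood-based mixed model with the post-treatment and 3-month scores as outcomes, baseline GHQ-12 as covariate, and arm, visit and their interaction as terms;
- the 1-week contrast is secondary;
- the completers' analysis is a sensitivity analysis;
- subgroup examination by education, employment and severity is separate from the baseline adjustment in the primary model.

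If SPSS is kept, name its mixed-model procedure, so that women with one missing visit are not dropped by default.

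The cost is a few sentences. Baseline GHQ-12 is already collected at screening, and no visit, measure or change of software is needed. The change should be made before outcomes are compared by arm.
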